### Participant incentives

Participants are provided checks as incentives for completion of the follow-up data collection portion of this project to compensate for their time and effort. For survey completion: a $20 check is mailed after the 3-month telephone follow-up and $25 checks are mailed after each of the 6- and 12-month follow-up. For those providing saliva samples: those providing saliva samples in the clinic receive a $100 check at the end of visit, while those providing mailed samples will be sent a $75 check upon receipt of the mailed saliva sample.

### Process measures

To ensure that the study protocol is implemented with fidelity, systems- and records-based data are collected on an ongoing basis. Process measures fall into three areas: (1) recruitment and retention; (2) intervention delivery and dose; and (3) staff productivity. Study investigators review reports monthly to monitor study activities and make recommendations for remediation as needed. Reports include the proportion of patients participating (or lost) at each level of screening and study activity (Figures 
1 and 
2). Intervention delivery and dose data collected include website log-ins, tailored e-messages sent, secure messages generated, and post-hospitalization telephone call receipt. Quit Staff manually enter the telephone call information into the website’s administrative portal while all other data are collected automatically by the website system. Staff productivity is monitored to ensure both protocol fidelity and timely completion of the study. These data include contact rates by the Quit Staff (bedside/telephone registrations and follow-up phone calls) and individual recruitment and retention rates for each study staff. Ongoing performance feedback from the Study Coordinator is provided to staff with appropriate recommendations.

**Figure 2 F2:**
[figure not shown]
Study flow diagram from enrollment to analyses.

### Sample size estimate

We have estimated the total number of participants recruited during the 22-month recruitment phase of this study as 1,488 based on published and UAB-specific information. Given published findings that smoking rates among hospitalized patients exceed general population rates 
[4,5,32-35], the estimated current rate of smoking in Alabama (22.5%) 
[2], and the UAB Hospital 2009 data (24% to 32%, depending on the ICD-9 codes used to define current smokers), we estimate that at least 24% of UAB Hospital inpatients will be current smokers. Among hospitalized smokers in other studies, 60% to 82% desired to quit and expressed willingness for post-hospitalization smoking cessation contact 
[4,33,36]. Almost 62% of Alabama households have internet access 
[15]; we anticipate 50% of our hospitalized patients who smoke will have internet access, given the likelihood of being from a lower socioeconomic status. Based on current admission trends, we expect an average of 10 new patients to meet eligibility criteria on a typical day within the 27 PCAs targeted, with at least half willing to receive information about the study. It is anticipated that the study population’s demographics and reasons for hospitalization will mimic the general population of hospitalized smokers at UAB Hospital (based on 2009 hospital data): 60% male, 43% African American, 1.5% Hispanic, 1.3% Asian, and <1% of other racial/ethnic background, with approximately 17% having acute myocardial infarction (AMI), pneumonia, and/or congestive heart failure (CHF).

### Power estimate

Power is estimated for the primary outcome: differences in self-reported smoking abstinence rates between the two treatment conditions at 6 months post-hospitalization based on 30-day point prevalence. Rates for smoking cessation reported in the literature for ‘usual’ post-hospitalization care are 5% to 15% at 6 months and 7% to 10% at 1 year 
[37]. With 1,488 participants, 744 assigned to each treatment condition, using 12% as an estimated rate for the comparison group, this study will be powered (β = 80%-type II error, α = 0.05-type I error) to detect a difference of 5.12% between the two treatment conditions (two-sided). For the intervention condition, a sub-analysis between the group with one of three diagnoses (CHF, AMI, or pneumonia-expected *n* = 256) and the group with all other diagnoses (expected n = 488) will have sufficient power (β = 80%-type II error, α = 0.05-type I error) to detect a difference in tobacco abstinence rates of 9.4% (two-sided), assuming the three-diagnoses comparison group has a 25% quit rate (two-sided). Note that, as the smoking cessation rate increases for the comparison group, a larger difference is necessary between groups to achieve a specific level of power, which is why a higher rate is used for power computation. The reverse of this is true as well: as the comparison group rate decreases, a smaller difference between groups achieves the same level of power.

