### Data analyses

#### Primary and secondary outcomes analyses

The study analyses will be conducted using the most up-to-date version of SAS (SAS Institute, Cary, NC, USA) and *P* ≤ 0.05 will be considered significant for all analyses, except where Bonferroni correction for multiple comparisons is necessary. Baseline characteristics of both groups will be compared to ensure that random assignment results in comparable groups. Any factors not found balanced across randomization groups will be adjusted for in subsequent models. Continuous variables will be compared using a two-sample t-test, while a chi-square test of association will be used to compare categorical variables.

The primary outcome for this study will be self-reported 30-day tobacco abstinence rates at 6-months follow-up. For missing outcome data at the 6- and 12- months follow-ups, we will impute missing data using a propensity-based multiple imputation method 
[38] that has been agreed upon for the collaborative 
[39]. This approach assumes that non-response is random which is more robust than assuming all non-responders are smokers 
[40]. Using baseline and any additional available data (for example, 3-month survey), we will use a logistic regression model to estimate the propensity to respond to the follow-up survey for each hospital stratum and treatment arm combination. Within each combination we will stratify further based on values of the estimated propensities and then impute a value for the outcome for each non-respondent by randomly sampling from the respondent values within their sub-stratum. Multiple datasets will be created and the point estimates and the estimated standard error from each dataset will be combined to arrive at a single point estimate, its estimated standard error, and the associated confidence interval or significance test 
[40]. Given the potential for missing data not-at-random, we will further implement a pattern-mixture analyses 
[41] based on content experts and the observed patterns of missing data.

We will also run a responders-only analysis for descriptive purposes. A two-sample test for the difference in proportions will be used to test whether the quit rates are different between the two treatment conditions (two-sided) and, if indicated, whether the Decide2Quit intervention is effective in promoting smoking cessation compared to the usual care group (one-sided). We will conduct this same statistical analysis for secondary outcomes.

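### The stated 80% power for a 5.12-point difference needs a 6-month outcome from every assigned patient, and the analysis section plans for missing ones

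*Protocol article*

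**What the plan says.** The Sample size estimate section derives the total from admissions, smoking prevalence and internet access, and presents it as a recruitment forecast: "We have estimated the total number of participants recruited during the 22-month recruitment phase of this study as 1,488".

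The Power estimate section takes that total as the basis for power: "With 1,488 participants, 744 assigned to each treatment condition, using 12% as an estimated rate for the comparison group, this study will be powered". The outcome is self-reported abstinence "at 6 months post-hospitalization based on 30-day point prevalence". The claim is "this study will be powered (β = 80%-type II error, α = 0.05-type I error") "to detect a difference of 5.12% between the two treatment conditions (two-sided").

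The Data collection and measurements section says that follow-up outcomes are obtained by telephone interview after discharge. The Primary and secondary outcomes analyses section then provides for outcomes that are not obtained: "For missing outcome data at the 6- and 12- months follow-ups, we will impute missing data using a propensity-based multiple imputation method". Imputed values are drawn at random from respondents in the same hospital stratum, treatment arm and response-propensity class, and the estimates and standard errors are combined across datasets. A pattern-mixture analysis and a descriptive responders-only analysis are also planned. The text shown gives no expected 6-month response rate.

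**The concern.** The power statement and the analysis section rest on different data. The first counts every assigned patient as contributing a 6-month outcome. The second provides for patients who do not. If 744 per arm is just the number of complete outcomes that 80% power requires, there is no reserve, and the stated power is the best case rather than the expected one.

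At stake is the headline design property for the primary outcome. A reader who meets a null result will take from this sentence that the trial had 80% power against a difference of about 5 points. With incomplete follow-up, and control abstinence at the planned 12%, the trial would have had less.

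**Working it through.** **Inputs from the protocol article.** Control rate p1 = 0.12; difference 0.0512, so p2 = 0.1712; n = 744 per arm; two-sided alpha 0.05 (z = 1.960); 80% power (z = 0.842). The planned test is a two-sample test of proportions.

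**Input that is assumed.** The proportion d of 6-month outcomes that are missing, equal in both arms, from 5% to 30%.

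**Formula.** Pooled two-proportion normal approximation without continuity correction. With p̄ = (p1 + p2)/2 = 0.1456:

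- SE0 = √[2p̄(1 − p̄)/n] under the null
- SE1 = √{[p1(1 − p1) + p2(1 − p2)]/n} under the alternative
- Power = Φ[(p2 − p1 − 1.960 × SE0)/SE1]

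**Step 1: reproduce the stated figure.** At n = 744, SE0 = 0.01829 and SE1 = 0.01824. Power = Φ[(0.0512 − 1.960 × 0.01829)/0.01824] = Φ(0.842) = 80.0%.

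In the other direction, the required n is (1.960 × 0.4988 + 0.842 × 0.4975)²/0.0512² = 1.950/0.002621 = 743.8, or 744 per arm. The match is exact, so the implied missing rate is 0%. Other versions of the formula leave no useful reserve: unpooled and arcsine both give 80.2% at n = 744, and a continuity correction gives 77.9%.

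**Step 2: replace assigned patients with responders.** Take n = 744(1 − d), rounded down, in the same formula.

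| Missing at 6 months (assumed) | Responders per arm | Power for 5.12 points | Detectable difference at 80% power |
|---|---|---|---|
| 0% | 744 | 80.0% | 5.12 points |
| 5% | 706 | 77.9% | 5.27 points |
| 10% | 669 | 75.7% | 5.42 points |
| 20% | 595 | 70.7% | 5.78 points |
| 30% | 520 | 64.9% | 6.22 points |

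**Step 3: ask whether the planned imputation restores the lost power.** Values drawn from same-arm respondents repeat information already in the data, and the combined standard error carries the between-imputation variance. A simulation of this type of procedure (744 per arm, 12% against 17.12%, five propensity classes unrelated to outcome, 20 imputations, 2,000 trials per scenario) gave power of 75%, 71% and 64% at 10%, 20% and 30% missing. These are close to the responder-only values of 75.7%, 70.7% and 64.9%. Classes that also predict quitting could recover a little, but not the full 744.

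**Step 4: check the alternative that the plan rejects.** If all non-responders were counted as smokers, both rates would shrink by the factor (1 − d) with n kept at 744. Power would be 75.0%, 69.3% and 62.8% at 10%, 20% and 30% missing, so that does not rescue the figure either.

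**The case against.** **The number is correct.** It is, for 744 complete outcomes per arm. Nothing is miscalculated. The fault lies in attaching the figure to patients assigned.

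**An attrition allowance may sit in the full protocol or in the study flow figure, which is not shown.** This is fair as far as it goes: an article may omit an allowance, and one cannot say that none exists. But the article prints a power figure, ties it expressly to the number assigned, and that figure leaves room for no loss. An allowance stated elsewhere would not make the sentence right.

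**Uncertainty in the control rate matters as much.** The plan cites 5% to 15% for usual care at 6 months. By the same formula, a 10% control rate gives 84.7% power for 5.12 points with full data, 80.7% with 10% missing and 76.0% with 20% missing. An 8% rate still gives 82.0% with 20% missing. A 15% rate gives only 73.8% with full data. This stands as a limit: the shortfall is shown at 12% and not at every plausible control rate. It does not excuse the sentence, which fixes 12%.

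**A null result is judged by its confidence interval.** True, and the plan provides one from the combined imputations. The power sentence does not decide what is excluded, so the consequence lies in how the design is described.

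**A reader might infer that the true power is 65% to 76%, or that the plan expects heavy non-response.** The text supports neither. That range is only what an assumed 10% to 30% loss produces. Provision for missing data is routine and implies no particular rate.

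**Conclusion.** The concern holds in a conditional form. At a 12% control rate and two-sided 0.05, 80% power for 5.12 points requires 744 observed outcomes in each arm, and 744 is the number assigned. Any missing 6-month outcomes take power below 80%, and the planned imputation recovers little of the loss.

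The direction is firm. The size is not, because it rests on a response rate that the text does not give. Across the assumed range of 5% to 30% missing, power for 5.12 points runs from about 78% down to 65%, and the detectable difference from about 5.3 up to 6.2 points. The calculation also assumes equal loss in the two arms and little association between propensity class and quitting.

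It does not follow that the trial is too small. The total reflects what can be recruited, and the power section reports what that total can detect. Nor does labelling 80% as the type II error add weight: it is a slip, with no effect on any figure. This should be fixed as a reporting correction. It is not a defect that stops the trial or changes its analysis.

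**What to change.** Keep the total at 1,488. In the Power estimate section, state the expected 6-month response and give the power or detectable difference on the expected number of responders. For example, if 80% respond, 744 × 0.80 = 595 per arm, which gives 80% power for 5.8 points and 71% power for 5.12 points. A short range of response rates would serve if no single rate can be defended.

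In the same sentence, and in the diagnosis sub-analysis sentence that repeats the label, write power = 80% (β = 20%).

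The cost is a text change and a slightly less favourable stated figure. No extra patients and no change to the analysis are needed.

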### Data analyses

#### Primary and secondary outcomes analyses

The study analyses will be conducted using the most up-to-date version of SAS (SAS Institute, Cary, NC, USA) and *P* ≤ 0.05 will be considered significant for all analyses, except where Bonferroni correction for multiple comparisons is necessary. Baseline characteristics of both groups will be compared to ensure that random assignment results in comparable groups. Any factors not found balanced across randomization groups will be adjusted for in subsequent models. Continuous variables will be compared using a two-sample t-test, while a chi-square test of association will be used to compare categorical variables.

The primary outcome for this study will be self-reported 30-day tobacco abstinence rates at 6-months follow-up. For missing outcome data at the 6- and 12- months follow-ups, we will impute missing data using a propensity-based multiple imputation method 
[38] that has been agreed upon for the collaborative 
[39]. This approach assumes that non-response is random which is more robust than assuming all non-responders are smokers 
[40]. Using baseline and any additional available data (for example, 3-month survey), we will use a logistic regression model to estimate the propensity to respond to the follow-up survey for each hospital stratum and treatment arm combination. Within each combination we will stratify further based on values of the estimated propensities and then impute a value for the outcome for each non-respondent by randomly sampling from the respondent values within their sub-stratum. Multiple datasets will be created and the point estimates and the estimated standard error from each dataset will be combined to arrive at a single point estimate, its estimated standard error, and the associated confidence interval or significance test 
[40]. Given the potential for missing data not-at-random, we will further implement a pattern-mixture analyses 
[41] based on content experts and the observed patterns of missing data.

We will also run a responders-only analysis for descriptive purposes. A two-sample test for the difference in proportions will be used to test whether the quit rates are different between the two treatment conditions (two-sided) and, if indicated, whether the Decide2Quit intervention is effective in promoting smoking cessation compared to the usual care group (one-sided). We will conduct this same statistical analysis for secondary outcomes.

Several covariates may affect the relationship between the intervention effect and the quit rate. Potential covariates include age, tobacco dependence, major health issue, number of diagnostic codes assigned at hospital discharge, race, smoking history, alcohol use, depressive symptoms, social support, use of other smoking cessation programs, and self-efficacy. Because participants are randomized to treatment arm, these potential covariates will theoretically be balanced across the two arms. However, the strength of the association between each of these covariates and the quit rate will be assessed in a logistic regression model. This analysis will provide the variables that are predictive of smoking cessation among all smokers and can be repeated to test for predictors among the three diagnostic groups (AMI, pneumonia, and CHF) *vs* all other diagnostic groups. Secondary exploratory analyses are planned to investigate a range of broader issues related to smoking cessation. An analysis similar to the primary analysis will test potential differential effects of the Decide2Quit intervention among diagnostic groups by comparing those patients with AMI, CHF, and/or pneumonia to patients not having these diagnoses. A third set of tests of proportions will compare each of the three diagnostic groups of interest in the intervention condition to their matching group in the usual care condition (although power will be limited due to small sample sizes). The relationship between dose and smoking cessation will be examined using logistic regression tests, as we expect dose will not be normally distributed.

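### Covariates for the adjusted models are chosen by significance-testing baseline differences between randomised arms, so chance rather than prognostic value sets the adjustment

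*Protocol article*

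**What the plan says.** All of this is in the protocol article, Data analyses, under Primary and secondary outcomes analyses.

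- Purpose of the check: "Baseline characteristics of both groups will be compared to ensure that random assignment results in comparable groups".
- Rule that follows from it: "Any factors not found balanced across randomization groups will be adjusted for in subsequent models".
- Tests used: "Continuous variables will be compared using a two-sample t-test, while a chi-square test of association will be used to compare categorical variables".
- Threshold: P ≤ 0.05 "will be considered significant for all analyses, except where Bonferroni correction for multiple comparisons is necessary". No other definition of imbalance is given.
- Test for the primary outcome, repeated for the secondary outcomes: "A two-sample test for the difference in proportions will be used to test whether the quit rates are different between the two treatment conditions". It carries no covariates.
- A later paragraph of the same section lists 11 possible covariates, beginning "Potential covariates include age, tobacco dependence, major health issue, number of diagnostic codes assigned at hospital discharge, race, smoking history, alcohol use, depressive symptoms" and continuing with social support, "use of other smoking cessation programs, and self-efficacy". Their association with quitting is examined in a logistic model, as an analysis of predictors. The article does not say that this analysis chooses the adjusters.
- The same paragraph acknowledges: "Because participants are randomized to treatment arm, these potential covariates will theoretically be balanced across the two arms".

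Under Participant recruitment and randomization to condition, allocation is blocked within each patient care area (PCA).

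**The concern.** A baseline significance test in a randomised trial tests a hypothesis already known to be true: apart from chance, the arms come from the same population. At the 0.05 level each factor has a 5% chance of being flagged, whether or not it predicts quitting. A covariate earns its place in a model by its association with the outcome, and the rule ignores that association.

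Two things are at stake. The adjusted model cannot be written down before the data are seen, and most of the benefit available from adjusting for real predictors is given up. There is also a gap in priority. If an imbalance is found there will be an unadjusted and an adjusted result, and nothing says which one leads.

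**Working it through.** **1. The plan's own sample size (Power estimate section).** Inputs: 12% against 17.12% (12% + 5.12 points), two-sided α = 0.05, power 80%. The pooled-variance formula is

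n = [z₀.₉₇₅ √(2p̄q̄) + z₀.₈₀ √(p₁q₁ + p₂q₂)]² / d², with p̄ = 0.1456 and d = 0.0512.

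- 1.960 × √0.2488 = 0.9776
- 0.8416 × √(0.1056 + 0.1419) = 0.4187
- n = (1.3963)² / 0.002621 ≈ 744 per arm

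The stated 744 per arm (1,488 in total) reproduces. It rests on an unadjusted comparison, so nothing below changes it.

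**2. How often the rule fires.** For k independent factors tested at 0.05, the expected number of flags is 0.05k and the chance of at least one is 1 − 0.95^k.

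| Factors tested | Expected flags | Chance of at least one |
|---|---|---|
| 11 (named in the article) | 0.55 | 1 − 0.569 = 43% |
| 20 (assumed) | 1.0 | 1 − 0.358 = 64% |
| 30 (assumed) | 1.5 | 1 − 0.215 = 79% |

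Thirty is reached only by counting separately the 16 items in Table 2's demographics row and adding the 14 other rows marked at month 0. If a Bonferroni correction were applied to 11 tests, the chance would be 1 − (1 − 0.05/11)^11 ≈ 5%. The article does not say whether the balance tests are among those corrected.

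**3. What the rule selects.** A given predictor of quitting, however strong, is left out with probability 95%. With two true predictors, the chance of picking up either is 1 − 0.95² = 9.75%.

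**4. Effect on power and error.** A simulation used 3,000 trials per scenario, 744 per arm and 11 independent covariates, of which 2 were prognostic. The treatment effect was tested in logistic models. The covariate effects are assumptions: log-odds of 0.6 and 0.3 per SD (moderate), or 1.0 and 0.6 per SD (strong).

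| | No adjustment | Baseline-test rule | Prespecified, 2 predictors |
|---|---|---|---|
| Power, moderate | 78.8% | 78.9% | 81.3% |
| Power, strong | 80.1% | 80.8% | 87.3% |
| Type I error, moderate | 5.8% | 5.7% | 6.1% |
| Type I error, strong | 5.3% | 5.1% | 5.2% |

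Monte Carlo standard errors are about 0.7 points for power, √(0.8 × 0.2/3000), and 0.4 points for type I error, √(0.05 × 0.95/3000). At least one covariate was flagged in 42% to 45% of trials. About 82% of the flagged covariates were non-prognostic, as expected when 9 of the 11 are.

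**5. What is being estimated.** Under the alternative, the mean treatment log-odds ratio was 0.414 unadjusted and 0.440 with prespecified adjustment (moderate), and 0.419 and 0.492 (strong). A logistic treatment effect depends on which covariates are in the model, so the choice of set bears on the meaning of the estimate as well as on power.

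**The case against.** The strongest reply is that the primary result is not touched. The named test is unadjusted, the trial is powered on that comparison, and the balance rule reaches only later models. This stands. A reader might infer that the headline effect and its P-value come from a screened model, but the article does not say so. What remains open is which result leads once an imbalance is found.

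A reader might also infer that nominal error rates fail. The simulation does not support that: type I error was 5.1% to 5.7% under the rule and 5.3% to 5.8% without adjustment.

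A third tempting reading is that follow-up values of self-efficacy, social support or use of other programmes would be adjusted for, which would remove part of the intervention effect. Table 2 does measure self-efficacy, social support and cessation treatments at 6 and 12 months as well as at month 0. But the balance rule concerns baseline characteristics, the list of 11 belongs to a separate predictor analysis, and the remark that these covariates are balanced by randomisation makes sense only for baseline values. Adjustment for follow-up values is therefore not a stated plan. The wording merely fails to exclude it.

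Finally, the 64% to 79% range needs 20 to 30 independent factors, and Table 2's items overlap (diagnosis codes, DRGs and procedure codes, for example). The 43% for the named covariates is the better-supported figure. It too assumes independence and no Bonferroni correction.

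None of this defends the rule. It is stated outright rather than left to an analysis plan, and under it power was essentially that of no adjustment at all.

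**Conclusion.** The point holds for the adjusted models. The article fixes a poor selection rule: chance differences decide the covariates, and prognostic strength has no part in the choice. The demonstrated harm is a model that depends on the data and forgone precision. Power is lower by roughly 2 points under moderate assumed covariate effects and by about 6 to 7 points under strong ones; the true strength of these predictors is not given in the article. Neither bias nor material inflation of type I error has been shown, and the sample size is unaffected. The missing order of priority between the unadjusted and adjusted results is part of the same defect and should be settled with it.

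**What to change.** 1. Delete the baseline significance tests and the rule that links adjustment to them. Describe baseline characteristics by arm without P-values.
2. Prespecify a short set of known predictors of quitting, using month-0 values only, together with PCA as the randomisation stratum. Use it in every adjusted model whatever imbalance is observed. Items that may be recorded after randomisation, such as the number of discharge codes or use of other programmes during follow-up, should not enter by default.
3. State whether the unadjusted or the adjusted estimate is primary, and on what scale the adjusted effect is reported.

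The cost is a change of wording, with no change to data collection or sample size. There are two downsides. A chance imbalance in a factor outside the list is handled only in a sensitivity analysis. And with 27 PCAs averaging about 55 participants each (1,488/27), sparse areas may need pooling by a rule written in advance.
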